### Randomization and blinding

Participants in the randomized controlled trial will be assigned 1:1 to the intervention and control arms under restricted randomized block design (the block length is 4) after informed consent and collection of baseline data. The allocation sequence will be generated and released to the interventionist on a case-by-case basis by another independent department specializes in generating research random sequence. The recruitment staff have no access to the results of randomization prior to recruiting the subject. Participants will be informed of his group by a research assistant by phone. Interventionist, data collection staff, statistician are not the same persons. This is a single-blinded trial. The subjects cannot be blinded due to the nature of the intervention, and interventionist also acknowledge all those contacted are in the intervention arm. But anonymous responses will be entered into the database by a person unconnected with the project. The statistician will be blinded to individual result during the intervention period, and the allocation-to-trial-arm coding will not be revealed until dataset is sealed. The interventionist and supervisors will be blinded to the baseline and follow-up outcomes.

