### Phase 2: Effectiveness evaluation of the app-based intervention

#### Intervention description

Participants in the intervention arm will receive app-based intervention. Each of them will be required to download the app and register as a user consequently, their accounts information, e.g. account name, email address used for registration will be collected. Four disciplines will be taken into account during the intervention period: (1) Interaction: at least once interaction will be required between the user and the app per week (e.g., sexual risk behavior report). (2) Non-stigmatization: a supportive atmosphere including social, behavioral, and psychological support will be built, and all contents will be presented without sense of discrimination. (3) Motivation encouragement: design and development of the app, information offered by the app will be in line with users’ needs, willingness and preferences so as to inspire their using motivation and maintain their adherence of the intervention. And two methods, health behavior goals setting according to the user’s sexual risk behavior, and exchange for free condoms with points earned by using the app regularly will be involved as incentive approaches to increase individual’s motivation of behavior change. (4) User-experience-centric: the app-based intervention will be user-oriented and we lay emphasis on user experience from aspects of interface and function modules as well.

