#### Control group

For the control arm participants, each of them will be asked to build connection with the researcher through Wechat, the most widely used instant massaging app in China. They will receive usual care including free brochures of health information and free counseling services whenever they need. All of the participants will be promised of the confidentiality throughout the process.

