#### Participant follow-up

All of the subjects in control and intervention arms will attend four visits, one at baseline for screening and enrollment, three at 6-, 12-, 18-month respectively to assess their sexual and other health behaviors (detailed below). Any subject gets HIV infected during the whole study period will be referred to professionals for timely treatment and withdrawn form the study. Information and psychological counseling services, positive sex tips and necessary links to care resources will be provided by the study staff.

Figure 1 is the Participant flow chart of the study.

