#### Data collection

Baseline data of all the subjects will be collected at the enrollment procedure. The measures including demographic information (*age, marital status, current occupation, educational level, income and sexual orientation*), sexual behaviors (*number of male and female sex partners, frequency of sex, sex role, commercial sex behaviors, sex with fixed and casual sexual partners*), and health-related behaviors (*consistent condom use with multi-type of sex partners, regular HIV testing, drug use experience and sexual transmitted diseases infection history*).

For the rest three times of data collection, sexual behaviors, health-related behaviors, and app user experience (*user experience, feedback and suggestions*) during the last 6 months will be involved in an electronic questionnaire. One version will be made into the app and be delivered every 6 months to intervention arm participants. Another without app user experience items will be delivered by Wechat to the ones in control arm.

Data of cost of the intervention and participants’ app use behaviors will also be collected. Direct cost involves cost of development, operation and maintenance of this app and worker cost, indirect cost consists of participants’ expenses due to their joining in the study such as time spending, cell phone internet data and traffic cost. App use behaviors will be collected through the management system which involves participants’ use frequency and time durance, information scanned, interaction times and frequency.

We use the electronic questionnaire to make sure that all of the items will be presented in a logical order and necessary answers missing will not be allowed. The participant will be offered a non-cash financial compensation as phone bills worth 20 RMB for compensation every time he complete the data collection.

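### The follow-up behaviour questionnaire sits inside the app in one arm and goes by Wechat in the other, so self-reported outcomes are at risk of app-linked attrition and reporting bias

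*Protocol article*

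**What the plan says.** In the protocol article, Data collection has baseline measured the same way for everyone: "Baseline data of all the subjects will be collected at the enrollment procedure". At the three later time points, sexual behaviours, health-related behaviours and app user experience "during the last 6 months will be involved in an electronic questionnaire". The route then splits by arm. For the intervention arm: "One version will be made into the app and be delivered every 6 months to intervention arm participants". For controls: "Another without app user experience items will be delivered by Wechat to the ones in control arm".

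The Wechat contact is set up under Control group, for controls only: "each of them will be asked to build connection with the researcher through Wechat". Intervention description asks for app registration details, including an email address, but no Wechat link.

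Participant follow-up says: "All of the subjects in control and intervention arms will attend four visits". The later three visits, at 6, 12 and 18 months, are to assess behaviours, with a pointer to detail further on. That detail is the remote questionnaire.

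Outcome measures lists HIV/STDs infection as primary, and condom use and adherence to regular HIV testing as secondary. Intention-to-treat (ITT) plans EM imputation, a repeat with multiple imputation, and a propensity model for attrition.

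**The concern.** In the intervention arm the measuring instrument is part of the treatment. A man who deletes the app or stops opening it also loses the only questionnaire route the article gives him. A control who is indifferent to the trial may ignore Wechat, but Wechat is not the treatment under test, so his silence is not mechanically linked to adherence.

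If men who stop the app use condoms or test less than men who continue, the observed intervention arm is enriched for continuers. The comparison then moves towards app adherers against all responding controls, which favours the app.

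The setting differs too. Intervention participants answer inside a tool that sets behaviour goals and gives points for regular use, exchangeable for condoms. Controls answer through a messaging link to the researcher. Either setting may shape self-report, and not necessarily equally.

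At stake are the secondary behavioural comparisons and the cost-effectiveness ratios per 10% gain in condom use or testing. An STD outcome is also exposed if it is taken from the questionnaire, because Data collection lists STD history among the health-related behaviours.

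**Working it through.** **1. The plan's own figures.** Sample size and calculation gives a two-sided α of 0.05, power of 0.90, effect size 0.25, 336 per arm, and 400 per arm for one common 20% loss. Reading 0.25 as a standardised mean difference, n = 2 × ((1.960 + 1.282) / 0.25)² ≈ 336.2, which reproduces 336. The plan gives no separate loss for app stoppers, no stopping rate, and no outcome gap between stoppers and continuers.

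**2. Is the main harm lost power?** Power = Φ(0.25 / √(1/n_C + 1/n_I) − 1.96), starting from 400 per arm. The unequal loss rates are assumptions.

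| Control loss | Intervention loss | n_C / n_I | Power |
|---|---|---|---|
| 20% | 20% | 320 / 320 | 88.5% |
| 20% | 30% | 320 / 280 | 86.3% |
| 20% | 40% | 320 / 240 | 83.3% |

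The power cost is modest, so the issue is bias.

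**3. Size of the bias.** Let s be the share of the intervention arm who stop the app, c the rate of consistent condom use among continuers, and g the shortfall among stoppers.

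- Full-arm rate = (1 − s)c + s(c − g) = c − s·g
- Observed rate if only continuers answer = c
- Spurious gain = c − (c − s·g) = s·g

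This assumes that every stopper is missing, control loss is unrelated to outcome, and imputation recovers nothing. With assumed s of 10–40% and g of 10–20 points:

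- 0.10 × 0.10 = 1 point
- 0.25 × 0.20 = 5 points
- 0.40 × 0.20 = 8 points

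**4. Effect on a test.** Assume no true effect, a 50% rate in both full arms, and controls losing 20% at random (n_C = 320). Then n_I = 400(1 − s), the observed intervention rate is 0.50 + s·g, and SE = √(0.25/320 + p_I(1 − p_I)/n_I). The two-sided rejection probability is 1 − Φ(1.96 − s·g/SE) + Φ(−1.96 − s·g/SE).

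| s | g | Spurious difference | Rejection (nominal 5%) |
|---|---|---|---|
| 10% | 10 points | 1 point | 6% |
| 10% | 20 points | 2 points | 8% |
| 20% | 10 points | 2 points | 8% |
| 20% | 20 points | 4 points | 17% |
| 25% | 20 points | 5 points | 24% |
| 40% | 10 points | 4 points | 16% |
| 40% | 20 points | 8 points | 47% |

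For example, with s = 0.20 and g = 0.20: n_I = 320, p_I = 0.54, SE = 0.0395, and 0.04/0.0395 = 1.01. Rejection is 17%.

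**5. Do the planned methods deal with it?** EM and ordinary multiple imputation assume data missing at random given what is recorded. Run within arm, with baseline, earlier waves and app-use logs as predictors, they can recover part of the loss. But if answering requires the app, few or no respondents come from among the stoppers, so their values are extrapolated from continuers. The attrition propensity model also relies on recorded predictors. None of these can be relied on if stoppers differ in unrecorded ways.

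**The case against.** The case on the other side is substantial and limits the point.

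- **Visits exist for both arms.** Participant follow-up has everyone attending at 6, 12 and 18 months, and men are reachable by phone and email. Fallback procedures may stand in the full protocol. This means that loss on stopping the app is a risk, not a certainty. It does not remove the point, because the only collection route described for these visits is the arm-specific questionnaire.
- **Loss confined to one arm.** A reader might infer this. The documents do not support it: controls can also stop responding, and their silence may relate to behaviour. Only the link to treatment adherence is peculiar to the intervention arm.
- **Self-reports that cannot be compared at all.** This goes too far. Behaviour items, recall period, electronic format and payment match, and points reward app use rather than favourable answers. The Discussion already concedes bias from the open design. What remains is a difference of channel and context.
- **Imputation fails because controls have no app-use data.** This does not follow, since imputation can be done within arm. The real limit is data missing not at random.
- **The primary HIV outcome is compromised.** Inclusion and exclusion criteria has participants report test results to the researcher, and Setting names the local CDC as the body that verifies HIV status. Nothing confines HIV results to the app form.
- **The statistician is unblinded by the app-experience items.** The plan says "The statistician will be blinded to individual result during the intervention period" and withholds arm coding until the dataset is sealed. Nothing says that these items reach the statistician earlier, so this is speculation.

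**Conclusion.** The point holds in a limited form. As written, the article ties follow-up response to app use in one arm and states no app-independent route for men who stop. The self-reported comparisons of condom use, regular HIV testing and risk behaviour, and any STD outcome drawn from the questionnaire, are therefore at risk of differential, app-linked attrition and of context-dependent reporting.

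The size cannot be fixed from the documents. The 1–8 point range for consistent condom use rests wholly on assumed stopping rates and gaps, and on the three simplifying conditions in the working. The upper end is a worst case within that range. The direction favours the app only if stoppers do worse than continuers. The reporting component is not quantified.

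The change should be made before follow-up begins, because answers never collected cannot be recovered afterwards.

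**What to change.** 1. Send the same outcome questionnaire through the same app-independent channel, such as a Wechat link, to both arms at 6, 12 and 18 months. Include intervention participants who have stopped using or deleted the app.
2. Collect a Wechat contact from intervention participants at enrolment, as is already planned for controls.
3. Send the app-experience items afterwards as a separate form, and keep it out of the blinded outcome dataset.
4. Reconcile Participant follow-up, which describes attended visits, with Data collection, which describes remote delivery, so that it is clear what is collected where.

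The cost is one extra short form and one extra contact detail for the intervention arm. A Wechat version without the app-experience items is already planned, so no new outcome instrument is needed.

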#### Outcome measures

Outcomes will be compared between intervention and control arms, and between different time points of each arm. The primary outcomes include HIV/STDs infection rates, relative risk of HIV/STDs infection, secondary outcomes include condom use rates, adherence to regularly HIV testing. The incremental cost is defined as per HIV infection case decreased according to the app-based intervention, cost of every 1% decrease of HIV/STDs infection, or every 10% increase of consistent condom use and adherence to regularly HIV testing. Another outcome is the app-based intervention mechanism (detailed below).

#### Sample size and calculation

The intervention arm and control arm are of equal size and two-tailed hypothesis testing is assumed. Sample size is calculated by using the specific sample size function module PASS on the statistical analysis software NCSS [42]. By setting the α = 0.05, 1-β = 0.9, effect size as 0.25 [43], the sample size of each group is 336. With an estimated 20% loss to follow-up, 400 subjects are necessary for each group.

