## Background

Men who have sex with men (MSM) have been identified as high risk population of HIV infection and transmission since the world’s first AIDS case found in the United States at 1981 [1], and studies about HIV prevention among MSM had not been paid enough attention by Chinese researchers until the first case of AIDS patient in China found at 1985 [2]. HIV prevalence among MSM population has been continuously increasing at a rapid speed [3, 4]. In China, the proportion of HIV infection among MSM population jumped from 1.4% in 2001 to 6.3% in 2011 [5]. In 2007, MSM accounted for 12.2% among all of the yearly found new HIV infection cases, but this percentage soared to 29.4% in 2011 [6]. And in Changsha, Hunan Province of China, 46% of the yearly found new HIV cases are MSM (Changsha CDC). MSM have become the key population of HIV prevention interventions.

Despite scientists’ ongoing efforts to explore biomedical techniques of HIV prevention such as vaccine development, circumcision, antiviral drug use and so forth [7–9], behavioral interventions are still regarded as key approaches to HIV prevention [10, 11]. These involve regularly HIV testing, free condom providing, health education (e.g. peer education), individual behavioral and mental health counseling [12–17], etc. They have been proved to be effective of improving MSM’s health behaviors, finding newly infected individuals timely and referring them to rapid care and treatment services. Lots of existed studies involved an intervention package which consists of more than one way of behavioral intervention [18, 19]. However, since most of the interventions were performed by face-to-face patterns, there were three limitations which may constrain their effects. (1) High financial cost, labor consumption, and time consuming, (2) narrow coverage of MSM group, and (3) unsatisfying intervention adherence [20]. So it is imperative to explore more effective, extensively accessible, economic and comprehensive HIV prevention tools and strategies [21].

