#### Analysis of intervention outcomes

For intervention arm and control arm comparison, indicators of rates of HIV/STDs infection, consistent condom use, adherence to regularly HIV testing and sexual risk behaviors at baseline and at 6-, 12- and 18-month will be compared by using Chi-square test. And a COX risk model will be used for predicting HIV/STDs infection risks.

For the cost-effectiveness analysis, the total cost consists of direct and indirect cost mentioned above. Effectiveness covers the increased rates of consistent condom use and regularly HIV testing, the decreased rate of HIV/STDs infection, relative risk of HIV/STDs infection. A decision analytic model will be used to evaluate economic evaluation of the intervention. Using the estimated effectiveness and incremental cost of per HIV infection case decreased, every 1% decrease of HIV/STDs infection, every 10% increase of consistent condom use or adherence to regularly HIV testing, incremental cost-effectiveness ratio will be calculated.

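### The 90% power is stated for an effect size of 0.25 with no endpoint, scale or control risk, and it does not carry over to HIV infection alone

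*Protocol article*

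**What the plan says.** The Sample size and calculation section of the protocol article states that "The intervention arm and control arm are of equal size" and that "two-tailed hypothesis testing is assumed". It then sets α at 0.05 and power at 0.9 and continues: "effect size as 0.25 [43], the sample size of each group is 336". The allowance for attrition follows: "With an estimated 20% loss to follow-up, 400 subjects are necessary for each group". The section names no endpoint, measurement scale, control risk, target risk, hazard ratio or number of events.

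Under Outcome measures, "The primary outcomes include HIV/STDs infection rates, relative risk of HIV/STDs infection"; condom use and regular HIV testing are secondary. Under Analysis of intervention outcomes, infection rates at each visit "will be compared by using Chi-square test", and a Cox model is added. Only HIV-negative men may enter, so the HIV endpoint is new infection over 18 months. The one HIV frequency given for MSM nationally is in the Background: "the proportion of HIV infection among MSM population jumped from 1.4% in 2001 to 6.3% in 2011". That is the share of men infected, not the rate at which uninfected men become infected.

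**The concern.** A standardised effect has no fixed meaning for a binary outcome. The same 0.25 is a modest relative change when the control risk is near one half and a very large one when the event is uncommon. New HIV infection in men who test negative at entry may well be uncommon over 18 months. A reader who sees 90% power beside infection as the primary outcome will take the figure to cover HIV infection. If it does not, a non-significant HIV comparison could be taken as evidence that the app does not work, when the trial had little chance of detecting even a halving. HIV infection matters in its own right here: reducing it is a stated objective, and one of the cost-effectiveness measures is cost per HIV case averted.

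**Working it through.** **Inputs from the article.** Two-sided α = 0.05, power 0.90, effect size 0.25, 1:1 allocation, 336 per group, 20% loss, 400 per group enrolled (all from Sample size and calculation).

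**Inputs assumed.** The 18-month control risk: 3% to 10% for HIV alone, and 20% to 30% for HIV and STDs counted together. The article gives neither. The value 6.3% is included for illustration only.

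**1. Reproducing 336.** For a standardised mean difference d, or for Cohen's h (the arcsine effect size for two proportions):

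n per group = 2 × (1.960 + 1.2816)² / 0.25² = 336.2.

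This agrees with the stated 336. Other readings do not: a one-sided test gives 275 per group, Cohen's w = 0.25 gives 168 in total, and a hazard ratio of 0.75 needs 508 events. No infection risk enters the calculation that fits.

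**2. Evaluable men.** 400 × (1 − 0.20) = 320 per arm. At 320, power for a standardised 0.25 is 88.5%, slightly below the stated 90%.

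**3. If 0.25 is Cohen's h.** p₂ = sin²[(2·arcsin√p₁ − 0.25)/2]:

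| Control risk p₁ | App-arm risk p₂ | Relative reduction |
|---|---|---|
| 3% | 0.24% | 92% |
| 5% | 1.0% | 80% |
| 6.3% | 1.65% | 74% |
| 10% | 3.8% | 62% |
| 20% | 11.0% | 45% |
| 30% | 19.3% | 36% |

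**4. Power for infection with 320 per arm.** The pooled test of two proportions corresponds to the planned chi-square test:

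power = Φ[(|p₁ − p₂| − 1.960 × SE₀)/SE₁], where SE₀ = √[2p̄(1 − p̄)/n] and SE₁ = √[(p₁(1 − p₁) + p₂(1 − p₂))/n].

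Example, 10% halved to 5%: p̄ = 0.075, SE₀ = 0.02082, SE₁ = 0.02073. Then (0.05 − 1.960 × 0.02082)/0.02073 = 0.44, and power is 67%.

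Example, 6.3% to 1.39%: p̄ = 0.03845, SE₀ = 0.01520, SE₁ = 0.01508. Then (0.0491 − 1.960 × 0.01520)/0.01508 = 1.28, and power is 90%.

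| Assumed control risk | Power for a halving | App-arm risk needed for 90% power | Relative reduction needed |
|---|---|---|---|
| 3% (HIV) | 25% | not reachable | – |
| 5% (HIV) | 38% | 0.74% | 85% |
| 6.3% (HIV, illustrative) | 47% | 1.39% | 78% |
| 10% (HIV) | 67% | 3.58% | 64% |
| 20% (HIV/STDs) | 94.5% | 10.8% | 46% |
| 30% (HIV/STDs) | over 99% | 19.0% | 37% |

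At 3%, power stays below 90% (about 88%) even if almost no infections occur in the app arm. For a 25% relative reduction in HIV, power is 9% at a 3% control risk, 14% at 6.3% and 20% at 10%.

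**The case against.** The strongest reply is that the primary outcome is written as HIV/STDs, not HIV. If the two are counted together, the control risk may be well above 10%. At 20% to 30% the trial has 94% power or more for a halving. This stands. A reader might infer that the trial cannot answer its primary question at all, but the article does not support that: it leaves open whether HIV is analysed separately or with STDs, and the shortfall shown here is mainly for HIV alone.

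A second reply is that 0.25 may have been meant as Cohen's h, which is an effect size for two proportions and fits a chi-square test. Neither the text nor the arithmetic rules this out. So one cannot conclude that the figure was chosen for the behavioural outcomes and not for infection; nothing in the article says so. Reading it as h does not remove the difficulty, however, because it still implies an HIV reduction of 62% to 92% for control risks from 10% down to 3%.

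Third, calling the required HIV reduction implausible would be a judgement resting on an assumed incidence. The article gives neither an 18-month incidence nor an expected app effect, and its 6.3% is a prevalence in a population from which the infected are excluded here. The required reductions can be stated; their implausibility cannot be derived from the article.

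Fourth, this is a condensed article, and the full protocol may name the endpoint and scale. That is possible. But the article does print a 90% power claim beside infection as the primary outcome, and its readers have only that.

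**Conclusion.** The point holds for HIV infection alone. The 90% power belongs to an effect size of 0.25 that is tied to no endpoint, scale or control risk. Across assumed 18-month HIV risks of 5% to 10%, with 320 evaluable per arm, 90% power requires a reduction of about 85% to 64%, and at 3% it is out of reach. For HIV and STDs combined at an assumed 20% to 30%, the required reduction is about 46% to 37%, a much smaller problem. All of these figures depend on assumed control risks and on 20% loss in each arm. This should be fixed, but it concerns how the power is stated and does not show that the design is unsound. That a null HIV result would be misread is a risk to guard against; the article does not say that it will be read that way.

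**What to change.** In Sample size and calculation:

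- State which endpoint and which scale the 0.25 refers to.
- Give the assumed 18-month control risk and the detectable difference with 320 evaluable per arm, separately for HIV and for HIV/STDs. For example, at an assumed HIV risk of 6.3%, the difference detectable with 90% power is 6.3% to about 1.4%. Label any such risk as an assumption, and do not present the 2011 prevalence as a documented incidence.
- Limit the 90% power claim to the endpoint and effect for which it holds.

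In Analysis of intervention outcomes, commit to reporting the HIV comparison with its confidence interval, and say that a non-significant result will not be read as no effect.

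The cost is wording and a less favourable power statement for HIV. No extra participants and no change of endpoint or test are needed.

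### The 20% loss allowance does not fit the stated sample size: 400 per group leaves 320 evaluable, not the required 336 (minor; wrong as written)

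*Protocol article*

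**What the plan says.** The whole calculation stands in the Sample size and calculation section of the protocol article. The arms are equal in size, and "two-tailed hypothesis testing is assumed". The base number is given as "By setting the α = 0.05, 1-β = 0.9, effect size as 0.25 [43], the sample size of each group is 336". The loss allowance follows directly: "With an estimated 20% loss to follow-up, 400 subjects are necessary for each group".

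The figure of 400 is not a misprint. The abstract and the Study design section both give 800 men in total, split evenly between the arms.

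The section on intention-to-treat analysis says that everyone randomised will be analysed, with missing endpoints imputed by the EM algorithm and the analysis repeated with multiple imputation. Nowhere does the article say that the 336 already allows for loss, or that participants with imputed outcomes count towards it.

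**The concern.** Four figures are stated together: 90% power, 336 per group, 20% loss and 400 per group. If 336 evaluable men per group are needed for 90% power and one in five is lost, the number randomised must be 336 divided by the retained fraction. 400 is below that.

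What is at stake is the accuracy of the sample-size justification. It would normally be carried into the results report, where any reader can check it in one line. Estimates, tests and analysis sets are not affected.

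**Working it through.** **Inputs**, all from Sample size and calculation: two-sided α = 0.05; power 0.90; effect size 0.25; equal arms; 336 per group before loss; 20% loss; 400 per group randomised. One assumption is added for the power figures only: that 0.25 is a standardised difference with the usual two-group formula. The article names neither a scale nor an endpoint for it.

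**1. Reproduce 336.** n per group = 2(z₀.₉₇₅ + z₀.₉₀)²/d² = 2(1.95996 + 1.28155)²/0.25² = 2 × 10.5074/0.0625 = 336.2. This matches the stated 336 apart from rounding (a strict round-up gives 337; the t-test version gives 337.2). A one-sided test would give 275, which does not match. So 336 is the number before any allowance for loss, and the standardised-difference reading fits it.

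**2. Apply the stated loss to 400.** 400 × (1 − 0.20) = 320 per group. Shortfall: 336 − 320 = 16, or 16/336 = 4.8%.

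**3. Number needed to keep 336.** 336/(1 − 0.20) = 420 per group, 840 in total. The plan is 20 per group (40 in total) below that.

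**4. Loss that 400 can absorb.** 1 − 336/400 = 0.16, so at most 16%.

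Steps 2 to 4 do not depend on the scale of the effect size.

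**5. Power at 320 per group (conditional on the assumption).** Φ(d√(n/2) − z₀.₉₇₅) = Φ(0.25 × √160 − 1.95996) = Φ(3.1623 − 1.9600) = Φ(1.2023) = 88.5%. The t-test calculation gives 88.4%. At 336 the same two calculations give 90.0% and 89.9%.

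**6. Detectable effect at 320 per group (same condition).** (1.95996 + 1.28155) × √(2/320) = 3.2415 × 0.07906 = 0.256, against 0.250 planned.

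**7. Possible origin of 400.** Multiplying by 1 + 0.20 gives 336 × 1.2 = 403.2, close to 400 but not equal to it. The article shows no working for this step.

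**The case against.** The strongest case on the other side has four parts.

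*The gap is trivial.* Power drops by about 1.5 percentage points, the detectable effect moves from 0.250 to 0.256, and 20% is itself only an estimate. At 16% loss or less the plan meets its target. This stands, and it is why the point is minor. A reader might infer that the trial is seriously underpowered or must enrol 840 men. The figures do not support either inference.

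*The power figure rests on an unstated scale.* This stands too. The text says only "effect size as 0.25", and the source cited for it is not available here. The figures of 88.5%, 88.4% and 0.256 are therefore conditional; 320, 420 and 16% are not.

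*The number of completers is not the information in every analysis.* Under Outcome measures the primary outcomes are HIV/STD infection rates and relative risk, and the analysis section plans chi-square tests and a Cox model. In a Cox model power depends mainly on events, and a man lost after 6 or 12 months still contributes follow-up time. This stands as a limit on the power figure: a reader should not take 88.5% as the power of the infection comparison. It does not rescue the sentence, whose own figures are head counts.

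*Imputation keeps all 400 in the analysis.* This does not stand. The plan adds a loss allowance on top of 336, so it treats lost men as not counting towards that number. Imputation also does not restore the information that was lost.

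It is tempting to say that the authors inflated by 1.2 instead of dividing by 0.80. That is plausible, but it gives 403.2, and rounding to a convenient total of 800 is equally possible. The cause cannot be established and the point does not need it.

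**Conclusion.** The sentence is wrong as written, and the error is minor. With 400 per group and 20% loss, 320 remain, 16 fewer than the 336 that the plan requires. To retain 336 would take 420 per group, and 400 is enough only for loss up to 16%. These statements follow from the article's own figures, and no other section reconciles them.

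The effect on power is about 1.5 percentage points (88.5% against 90%), provided that 0.25 is a standardised difference. That reading is supported by its reproducing 336 but is not stated in the article. Whether 0.25 is a suitable effect size for the infection outcomes is a separate question, and nothing here settles it.

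**What to change.** Keep 400 per group and replace the final sentence of Sample size and calculation with wording along these lines:

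> We will randomise 400 participants per group. This keeps the 336 per group required for 90% power if loss to follow-up is no more than 16%. At the estimated loss of 20%, 320 per group would remain and power would fall slightly below 90% (about 88%, if the effect size of 0.25 is a standardised difference).

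The condition in the last bracket should stay unless the authors state the scale of the 0.25; without it, the sentence would write into the protocol a scale that they have not given. If they prefer not to quote a power figure, the first two sentences and the figure of 320 are enough to make the text correct.

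Randomising 420 per group would also reconcile the figures, but a gap this small does not call for it. The cost of the restatement is a short edit and a slightly less favourable stated figure. The design, enrolment and analysis do not change.
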